#### Secondary outcomes

*Feasibility:* (1) Among all eligible patients, the proportion of patients (i) consenting to participate and (ii) completing all scheduled follow-up assessments. Reasons for non-enrollment of all eligible patients will be recorded (e.g., physician refusal, patient’s preference, inability to meet study timelines). (2) The proportion of patients in each group receiving the assigned extent of surgical resection according to the randomized allocation, as assessed by the volume of residual contrast enhancement in 1st post-operative MRI and compared to the preoperative MRI. Due to the pragmatic nature of this trial, we use intention to treat as a measure of supramaximal resection intent. We expect that as a group, these patients should have less enhancing residual volume in post-operative imaging. Reasons for failure to receive the assigned extent of surgical resection will be recorded (e.g., physician refusal, technical challenges).Preliminary *efficacy:* Assessment of the (1) overall survival and (2) progression-free survival based on the Modified Response Assessment in Neuro-oncology (mRANO) criteria [21]. The date of death will be obtained from hospital records, outpatient follow-up clinic notes, or provincial cancer registries. Progression-free survival will be measured based on the mRANO criteria [21] during regular interval clinical and MRI follow-up (according to each institution’s established practice) until death or 12 months after surgery.
*Safety:* (1) National Institute of Health Stroke Scale (NIHSS), (2) mRS, (3) EQ-5D, and (4) 30-day all-cause mortality. Utilizing three independent scales for the assessment of morbidity will ensure that we capture any objective neurological deficits along with their impact on function and quality of life. It will be critical to ensure that a supra-marginal resection does not lead to an increased 30-day mortality rate, which is a time frame that is most likely to be related to adverse surgical events.

Specifically, we will measure the changes at each assessment relative to preoperative baseline values in the following scales:

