The NIHSS at days 2 ± 1 and 30 ± 5 after surgery (conducted during in-person follow-up). The NIHSS is a validated tool for measuring neurological outcomes that was originally developed for rapid grading of stroke symptoms but has since been adopted in surgical clinical trials [9].The mRS (assessed either in-person or over the phone) at 6 and 12 months after surgery. The mRS provides a measure of global disability and has been widely used to assess the outcomes after stroke and other neurological problems. The scale consists of six grades from 0 (no symptoms) to 5 (severe disability); 6 indicates death [22].The EQ-5D (assessed either in-person or over the phone) at 6 and 12 months after surgery. The EQ-5D is a generic instrument used to measure health-related QOL, designed for self-completion by respondents (face-to-face or over telephone interview, also available in proxy version through caregiver). It has five dimensions: mobility, self-care, usual activities, pain or discomfort, and anxiety or depression. This tool rates the impact of disease on a scale of 0 to 1 with a lower score indicating a greater effect on the health.Where feasible, we will also attempt neuropsychological assessments pre- and post-operatively to detect the subtle differences potentially attributable to a supra-marginal resection.

iv)Health economics: The future definitive RCT will also assess the incremental cost-effectiveness ratio at 6 months. This will be analyzed to determine whether a supra-marginal resection has the potential to decrease societal costs in the long term. Cost data will be collected, in addition to the quality of life (EQ-5D) at 6 and 12 months, which would enable the calculation of the incremental cost-utility ratio (ICUR) of the two interventions. We plan to conduct a full-scale health economic analysis in the future large-scale trial, based on both direct (e.g., operating room, nursing, inpatient hospital stay) and indirect costs (e.g., potential loss of income) costs. Utilities will be calculated based on the EQ-5D, and cost-utility will be based on the perspective of the “idealized insurer”/third-party payer (e.g., the provincial government payer). Given the short survival of HGG patients, discounting will be at 1% with provisions for subgroup analyses.

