### Participant timeline

Both intervention and control treatments will terminate at the completion of the surgery. Subsequent treatments will be the same for both groups according to usual clinical practice.

The following clinical and radiological endpoints will be the focus of the larger randomized controlled trial, but will also be measured on all patients during this pilot trial:*Clinical*: (a) Neurological status (NIHSS) at days 2 and 30 after surgery [23]. (b) Mortality status at 30 days after surgery and every 3 months thereafter until last follow-up after surgery. (c) Disability (mRS) and quality of life (EQ-5D) at 6 and 12 months after surgery [24].*Radiological*: GAD-enhanced brain MRI will be obtained within 72 h after surgery (“first post-operative MR”) and at regular intervals according to each institution’s established practice. This is typically performed every 3 months, or sooner if clinically indicated. Additional post-operative MRIs will be conducted according to each institution’s protocol and reviewed centrally. Additional MRIs are permitted, as needed. Progression-free survival is defined as the number of days from the date of randomization to the date of earliest disease progression based on the mRANO criteria [24] or to the date of death due to any cause, if progression does not occur.

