#### Adherence to protocol

We will define successful adherence as follows:i)Documenting every scheduled clinical assessment on day 2, day 30, 6 months, and 1 year (if alive) in at least 90% of patients.ii)*Implementation of the study protocol* by measuring in at least 90% of enrolled patients the planned primary outcome measure for the larger trial (i.e., overall survival). This rate is comparable to the ability to obtain an outcome in previous large glioma studies [9]

Any reasons for non-adherence to the protocol will be recorded to improve the future larger trial. We will also capture the amount of personnel time required to screen for, consent, enroll patients, complete study procedures, and data collection for the first 5 patients at each site. A strategy to refine the final protocol for the full-scale trial based on the results of the each of above steps will be planned.

The decision to progress to the larger phase III RCT will be based on (1) reaching the primary feasibility target of recruiting at least an average of 1 patient per 2 months per year in each of 6 centers during 2 years of active study participation at each center and (2) no safety or ethical concerns are raised by the Data and Safety Monitoring Board (DSMB) that cannot be rectified. For the future trial, we plan to use overall survival difference (i.e., hazard ratio) to determine the relative efficacy of the interventions and will use data from the pilot study to estimate the required sample size. A meta-analysis assessing 6-month PFS has favored GTR over subtotal resection (STR) (relative risk (RR) 0.72) [7]. For a supra-marginal resection to have a meaningful impact on the survival of HGG patients, a similar improvement of 0.7 hazard ratio would be desired. We calculated that a total of 295 patients (247 deaths) would be required for the trial to have 80% power to detect a hazard ratio of 0.7 (base median overall survival of 14 months) at a two-sided alpha 5% level and planned average length of follow-up of 2 years. Based on our plan to recruit 10 Canadian sites for the phase III study, with an average annual enrollment rate per site of 6 subjects with 2 active surgeons, we anticipate meeting the full enrollment target within 5.5 years. Assuming that there are no major changes to the pilot protocol, we will include the patients’ data in this future larger RCT.

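### Scoring the mRS as change from baseline with death = 6 ranks some deaths as less harm than another patient's disability, and the schedule shows no preoperative mRS or EQ-5D from which to compute the change

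*Protocol article*

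**What the plan says.** Protocol article, Secondary outcomes (Safety), lists the NIHSS, mRS, EQ-5D and 30-day mortality. For the three scales it says that "we will measure the changes at each assessment relative to preoperative baseline values in the following scales". On the mRS it adds: "The scale consists of six grades from 0 (no symptoms) to 5 (severe disability); 6 indicates death". On the EQ-5D: "This tool rates the impact of disease on a scale of 0 to 1 with a lower score indicating a greater effect on the health". No value for death is given on the EQ-5D or the NIHSS.

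Participant timeline gives the timing as "Disability (mRS) and quality of life (EQ-5D) at 6 and 12 months after surgery". The Schedule of events marks the combined EQ-5D/mRS row only at 6, 12 and 24 months. The NIHSS row is marked at screening, days 1-3 and day 30.

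Adherence to protocol gives the control survival assumption for the future trial: "base median overall survival of 14 months". Under Statistical methods, secondary outcomes are descriptive and the pilot is said not to be powered for superiority.

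**The concern.** The mRS already has a place for death at the bottom of the scale, below every living grade. Subtracting the preoperative grade gives that up: the score for death then depends on how disabled the patient was before surgery, and a death can score below a survivor's decline. On a scale meant to show whether wider resection harms function, and read when a large share of patients have died, the order of outcomes should not depend on where the patient started.

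There is also a practical gap. A change needs a baseline, and the printed schedule shows none for two of the three scales.

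**Working it through.** The article gives no figure of its own on this point, so there is none to reproduce.

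**Inputs.** mRS 0-5 for the living and 6 for death, scored as change from the preoperative grade (Secondary outcomes). Median survival 14 months (Adherence to protocol); 13-16 months as the background range (Introduction). 36 patients per group (Sample size). Assumption: preoperative mRS lies between 0 and 3. The article gives no mRS limit; the eligibility criteria require a Karnofsky score of at least 60.

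**1. Scores under the stated rule.** Death = 6 − baseline; survivor = later grade − baseline.

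| Preoperative mRS | Score if dead | Living patients who score worse |
|---|---|---|
| 0 | +6 | none |
| 1 | +5 | none |
| 2 | +4 | 0 to 5 (+5) |
| 3 | +3 | 0 to 4 (+4); 0 to 5 (+5); 1 to 5 (+4) |

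Four death/survivor combinations are inverted. Six more tie: death from 3 with 0 to 3, 1 to 4 and 2 to 5; death from 2 with 0 to 4 and 1 to 5; death from 1 with 0 to 5. A death from grade 3 counts as half a death from grade 0 (3/6).

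**2. How many deaths are present when the scale is read.** Exponential survival: P(dead by t) = 1 − 2^(−t/median).

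- 6 months: 1 − 2^(−6/14) = 0.257, or 36 × 0.257 = 9.3 of 36 control patients (22.9% to 27.4% for medians of 16 to 13 months).
- 12 months: 1 − 2^(−12/14) = 0.448, or 36 × 0.448 = 16.1 of 36 (40.5% to 47.3%).

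The deaths that can be inverted are those from baseline 2 or 3. The article does not give that share. If it were 30% to 60% (assumption), then 16.1 × 0.30 = 4.8 to 16.1 × 0.60 = 9.7 of the 12-month control deaths would score +4 or less.

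**3. Does this carry through to the arm means?**

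- At a fixed baseline b, 6 − b exceeds f − b for every living grade f. Turning any survivor into a death therefore always raises that arm's mean change.
- Difference in mean change = difference in mean later grade − difference in mean baseline. With equal baselines, subtraction leaves the arm difference unchanged.
- Example: two arms of 36, nine patients at each baseline 0 to 3 (mean 1.5), all others unchanged. Arm X: six patients at grade 3 die, mean change 6 × 3/36 = 0.50, mean grade 2.00. Arm Y: six patients go from 0 to 4, mean change 6 × 4/36 = 0.67, mean grade 2.17. The gap is 0.17 either way, so it comes from averaging grades and not from the subtraction. Only the distribution shows six deaths against none.

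**4. Is there a baseline?** Secondary outcomes promises a change on three scales. The schedule has a preoperative mark for the NIHSS and none for the mRS or EQ-5D, and Participant timeline lists those two only after surgery.

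**The case against.** The best defence is that numeric subtraction is partly inferred. The article says changes will be measured; it does not prescribe a mean change. It reports categorical variables as frequencies and proportions, so a table of mRS grades would be compatible with it. That is fair, and it is one reason the point is minor. It does not remove it: change from baseline is the measure the text names, and with death coded 6 its literal result is the table above.

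Deaths are also visible elsewhere: "4) 30-day all-cause mortality" is its own safety outcome, mortality status is recorded every 3 months, and overall survival is analysed as time to event. This stands, and it limits the consequences.

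Three stronger readings are tempting, and the document does not support them.

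- *Fatal harm can look like better function on the mRS.* Step 3 shows that baseline subtraction does not produce this.
- *The dead are dropped from the EQ-5D and NIHSS.* The article does not say so. The nearest text, "Documenting every scheduled clinical assessment on day 2, day 30, 6 months, and 1 year (if alive) in at least 90% of patients", is an adherence criterion. A rule may sit in an analysis plan not shown here. Nor would change scoring be the cause, since a raw score is equally undefined for a dead patient. A survivors-only EQ-5D summary could flatter an arm with more deaths, but that is a risk to guard against and not a stated method. For the day-30 NIHSS, few deaths are expected (about 5% at 1 month on the same constant hazard), and 30-day mortality is reported separately.
- *A wrong-signed signal would pass to phase III.* Progression depends on recruitment and on safety or ethical concerns raised by the DSMB, and the future trial is sized on overall survival. Neither uses mRS or EQ-5D change.

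**Conclusion.** The point holds for the mRS and is minor. As written, the safety outcome misorders some deaths relative to disability in patients with a different baseline and gives identical deaths scores from +3 to +6. About 26% and 45% of control patients would be dead at the 6- and 12-month readings. This rests on a preoperative mRS range of 0 to 3 and on exponential survival with the article's 14-month median. How often the misordering would occur cannot be fixed from the document, because the baseline mRS distribution is not given.

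The missing preoperative mRS and EQ-5D in the schedule is a separate inconsistency with the promised change scores. It concerns the schedule as printed; the full protocol or case report form may collect them.

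**What to change.** - **mRS:** replace the numeric change with the full 0-6 distribution by arm at 6 and 12 months, death = 6. If a summary comparison is wanted, make it ordinal, adjusted for baseline mRS only if that is collected. The distribution itself needs no baseline.
- **EQ-5D:** at each visit show the number dead by arm beside the survivors' values, and label those values as conditional on survival. A version with death = 0 can be a sensitivity summary but should not be the main one, because it can hide functional loss. With 12-month survival of 0.552 v 0.660 (14-month median, hazard ratio 0.7) and an assumed control survivor score of 0.65, the arm means are equal when survivors of wider resection score 0.552 × 0.65/0.660 = 0.544, a loss of 0.106. The article also does not equate an EQ-5D of 0 with death.
- **Schedule:** either add a preoperative mRS and EQ-5D or drop the wording on change for those two scales.

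The cost is wording and one table per visit; deaths are already recorded. Adding the preoperative assessments would cost a short extra assessment per patient at screening.

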### Schedule of events

**Table Taba:** 

Evaluation	14 days prior to surgery/randomization (screening/enrollment)	Day 0: surgery day (randomization)	Days 1–3: post-OP 1^**st**^ assessment	Day 30 (± 5 days) 2^**nd**^ assessment	6 months (± 2 weeks) post-surgery 3^**rd**^ assessment Collect outcomes	12 months (± 1 month) post-surgery	24 months: annually after (until death, completion of the pilot phase, or lost to F/U)
*Eligibility criteria, medical history, demographics*	X						
*Neurological exam (NIHSS)*	X		X	X			
*MR scan*	X^1^			X ^1^	X^1^	X^1^	X^1^
*Concomitant meds (steroid/antiepileptic)*	X			X	X		
*Received randomly assigned treatment*		X					
*Pathology report*				X			
*Surgical report*				X			
*Adverse surgical* adjuvant tx** events*			X*	X*	X**	X**	X**
*Outcome assessment (clinical secondary outcomes) (EQD-5-mRS)*					X	X	X
*Death*				X	X	X	X
*Progression free survival*				X	X	X	X
*Timing of RTX*				X	X	X	X
*Timing of chemotherapy*				X	X	X	X

*These adverse events only relate to surgery

**These adverse events only relate to adjuvant radiation and/or chemotherapy

^1^These images are obtained through routine clinical practice

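### mRS and EQ-5D outcomes are defined as change from preoperative baseline, but no preoperative mRS or EQ-5D is scheduled; separately, the schedule table and the text disagree on the first post-operative MRI

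*Protocol article*

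**What the plan says.** **Definition.** In the protocol article, Secondary outcomes (Safety) names the NIHSS, mRS, EQ-5D and 30-day all-cause mortality. For the scales it then states that "we will measure the changes at each assessment relative to preoperative baseline values in the following scales".

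**Timing of mRS and EQ-5D.** The same section gives "The mRS (assessed either in-person or over the phone) at 6 and 12 months after surgery" and "The EQ-5D (assessed either in-person or over the phone) at 6 and 12 months after surgery". Participant timeline repeats "Disability (mRS) and quality of life (EQ-5D) at 6 and 12 months after surgery". The row "Outcome assessment (clinical secondary outcomes) (EQD-5-mRS" in the Schedule of events is ticked at 6, 12 and 24 months.

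**Timing of NIHSS.** The row "Neurological exam (NIHSS" is ticked at screening, days 1–3 and day 30.

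**MRI.** Participant timeline says "GAD-enhanced brain MRI will be obtained within 72 h after surgery", calls this the first post-operative scan and applies it to all pilot patients. Secondary outcomes (Feasibility) assesses the resection received from residual enhancement on the first post-operative MRI against the preoperative MRI. The MR row of the schedule is ticked at screening, day 30 and 6, 12 and 24 months, with the footnote "These images are obtained through routine clinical practice".

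**Link to data capture.** Data collection and management makes the case report form the primary data collection instrument and says that it will hold the information set out in the schedule of events.

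**The concern.** A change score needs two measurements. The outcome definition promises a preoperative value for all three scales, but the visit plan supplies one only for the NIHSS. Since the case report forms are built on the schedule, a site that follows the plan exactly would never collect a preoperative mRS or EQ-5D.

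The article relies on these two scales to show whether removing non-enhancing brain costs patients function or quality of life. Eligibility runs from a Karnofsky score of 60 upwards, so preoperative function will vary. With 36 patients per group, a chance imbalance at baseline could pass for surgical harm in the 6- and 12-month values, or could hide it. The loss is permanent for each patient operated on without a baseline. The article also intends to carry pilot patients into the phase III trial if the protocol does not change much, so the gap would go with them.

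The MRI discrepancy matters less. The scan that defines the extent of resection is required in the text but absent from the table that sites are likely to work from.

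**Working it through.** No sample size, power or event count enters this point, so there is no figure of the plan to reproduce. The check compares the visit lists.

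**1. Is the table intact?** Each of the three relevant rows has seven cells, matching the seven visit columns. The blanks are therefore blanks in the schedule and do not come from text extraction.

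**2. Ticks by visit in the Schedule of events**

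| Row | Screening | Day 0 | Days 1–3 | Day 30 | 6 mo | 12 mo | 24 mo |
|---|---|---|---|---|---|---|---|
| NIHSS | X | – | X | X | – | – | – |
| mRS / EQ-5D | – | – | – | – | X | X | X |
| MR scan | X | – | – | X | X | X | X |

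**3. Change from baseline, scale by scale**

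- NIHSS: baseline at screening, follow-up at days 1–3 and day 30. Computable.
- mRS: follow-up at 6 and 12 months (24 in the table), no baseline in the table or the text. Not computable as scheduled.
- EQ-5D: the same. Not computable as scheduled.

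Two of the three scales are affected, for all 72 planned patients.

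**4. Would the trial's own checks reveal the gap?** Adherence to protocol counts assessments at day 2, day 30, 6 months and 1 year. A missing preoperative assessment does not enter that count.

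**5. Extent of resection.** The preoperative MRI is ticked at screening. The post-operative scan is required within 72 h by Participant timeline, for all pilot patients. Both inputs therefore exist under the text, and the outcome is computable. Under the table alone, the first post-operative MRI tick is day 30, which does not match the 72 h definition.

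**The case against.** **The definition itself implies a baseline.** Stating that change from preoperative values will be measured could be read as a commitment to take them. The timing lists in the text name only follow-up times for every scale, including the NIHSS, which does have a screening tick. Silence in those lists therefore does not prove that no baseline will be taken. This stands as far as it goes: the documents show that none is scheduled, not that none will ever be collected. It does not rescue the table, which ticks a screening NIHSS and leaves the mRS/EQ-5D row blank in the same column.

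**An article condenses a fuller protocol.** That would answer an omitted detail. Here the article prints a complete visit schedule that does not deliver its own outcome definition.

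**Preoperative function is known from other measures.** The Karnofsky score is an eligibility criterion and the NIHSS is done at screening, so baseline imbalance can be examined and some adjustment is possible. This stands. Neither measure can supply an mRS or EQ-5D change score.

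**The stakes are limited.** The primary outcome is enrolment and allocation. The progression criteria rest on recruitment and on safety or ethical concerns raised by the DSMB, whose six-monthly reports are described as 30-day mortality and serious adverse events. Secondary outcomes are descriptive. This stands and lowers the severity.

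**The MRI tick at day 30 may mark retrieval of routine images.** Surgical and pathology reports are ticked there too, and the footnote refers to routine practice. This is plausible, but the table does not say so.

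**Conclusion.** The point holds for mRS and EQ-5D. As written, change from baseline cannot be computed for two of the three safety scales, and the gap cannot be repaired after surgery. Severity is moderate. The conclusion assumes that sites collect what the schedule and case report forms list and nothing more.

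A reader might infer more than the documents support:

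- *That all the change-from-baseline safety outcomes fail.* The NIHSS has a preoperative assessment, and 30-day mortality needs none.
- *That the extent of resection cannot be computed.* Participant timeline requires the 72 h scan in all pilot patients. The blank cell is a conflict between table and text, and it does harm only where a site works from the table alone.
- *That 72 change scores are lost per scale and visit.* The 72 counts patients without a scheduled baseline. The number of follow-up scores depends on survival and retention; with the stated median survival of 13–16 months, some patients will die before 12 months.
- *That a gain in precision from baseline adjustment can be quoted.* It would rest on an assumed correlation, and the pilot is descriptive and not powered for comparison.
- *That the cost-utility analysis is compromised.* The full economic analysis is assigned to the future trial; the pilot only collects data for it.

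**What to change.** 1. Add mRS and EQ-5D to the screening column of the Schedule of events and to the screening case report form, and name the preoperative assessment in Secondary outcomes and Participant timeline. The cost is a few minutes of questionnaire per patient at an existing visit and one form page. No new visit is needed.
2. If that is not adopted, restate the two outcomes as 6- and 12-month values and limit the change-from-baseline definition to the NIHSS. This costs nothing to run, but gives up the assessment of within-patient change in function and quality of life.
3. Reconcile the MR row with Participant timeline and with the resection-extent outcome, so that all three identify the same first post-operative scan, and say what the day 30 tick stands for. This is a textual correction.

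The first change is worth making before further patients are operated on. A functional assessment at day 30 and the choice of a baseline-adjusted analysis are matters of preference or for the analysis plan, and are not part of this point.

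### mRS and EQ-5D, named as safety scales for surgical deficits, have no scheduled preoperative or day 30 value, so early functional cost is captured only indirectly

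*Protocol article*

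**What the plan says.** Under Outcomes, Secondary outcomes, the safety list is NIHSS, mRS, EQ-5D and 30-day all-cause mortality. The protocol says that using three scales "will ensure that we capture any objective neurological deficits along with their impact on function and quality of life". It describes the first 30 days, when speaking of mortality, as a period "which is a time frame that is most likely to be related to adverse surgical events". It then promises: "Specifically, we will measure the changes at each assessment relative to preoperative baseline values in the following scales".

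The timings that follow are:

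- NIHSS: "The NIHSS at days 2 ± 1 and 30 ± 5 after surgery (conducted during in-person follow-up".
- mRS: "The mRS (assessed either in-person or over the phone) at 6 and 12 months after surgery".
- EQ-5D: "The EQ-5D (assessed either in-person or over the phone) at 6 and 12 months after surgery".
- Neuropsychology: "Where feasible, we will also attempt neuropsychological assessments pre- and post-operatively".

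Participant timeline repeats the NIHSS, mRS and EQ-5D times. In the Schedule of events, the row "Outcome assessment (clinical secondary outcomes) (EQD-5-mRS" is marked at 6, 12 and 24 months only. The NIHSS row is marked at screening, days 1–3 and day 30 only. Neuropsychological testing has no row. Adverse events at days 1–3 and day 30 are restricted to those of surgery. From 6 months on they are restricted to those of adjuvant radiation and chemotherapy.

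**The concern.** The main risk that the Introduction sets against a survival benefit is damage to functional brain tissue. Two of the three morbidity scales exist to turn a neurological deficit into its effect on daily function and quality of life. Neither is applied in the window that the protocol itself links most closely to surgery.

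The schedule also separates the instruments completely. NIHSS ends at day 30 and mRS and EQ-5D begin at 6 months, so a deficit and its functional impact are never recorded at the same visit. When mRS and EQ-5D are scored, no scheduled neurological scale or surgical adverse event item helps to attribute a poor score to the operation.

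The missing preoperative value is a second gap. Change from baseline is promised for each scale, but the schedule supplies a baseline for NIHSS only.

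These data cannot be recovered later. Participant timeline calls these endpoints the focus of the larger trial, and Adherence to protocol plans to carry pilot patients into it if the protocol does not change materially.

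**Working it through.** **Step 1. Set the schedule against the stated purpose** (Schedule of events, with Secondary outcomes and Participant timeline).

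| Measure | Screening | Days 1–3 | Day 30 | 6 mo | 12 mo | 24 mo |
|---|---|---|---|---|---|---|
| NIHSS | X | X | X | – | – | – |
| mRS, EQ-5D | – | – | – | X | X | X |
| Surgical adverse events | – | X | X | – | – | – |
| Adjuvant-therapy adverse events | – | – | – | X | X | X |

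Text and table agree that the first mRS and EQ-5D come at 6 months. This is therefore not a detail lost when the protocol was condensed into an article. Change from baseline needs a value in the first column of the mRS/EQ-5D row, and there is none.

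**Step 2. Inputs for the share of deaths.** Median survival is 13–16 months (Introduction) and 14 months as the base value for the future trial (Adherence to protocol). The target hazard ratio is 0.7 (same section). Group size is 36 (Sample size). Exponential survival is my assumption.

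The plan gives no figure for mRS or EQ-5D to reproduce. Its one power calculation, 247 deaths, does reproduce with the Schoenfeld formula: 4 × (1.960 + 0.842)² / (ln 0.7)² ≈ 247. So the hazard ratio of 0.7 is read as the sponsor meant it.

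**Step 3. Share dead by time t.** With no treatment effect, D(t) = 1 − 2^(−t/median).

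| Median | 1 month | 6 months | 12 months |
|---|---|---|---|
| 13 months | 5.2% | 27.4% | 47.3% |
| 14 months | 4.8% | 25.7% | 44.8% |
| 16 months | 4.2% | 22.9% | 40.5% |

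Per arm of 36, this is about 1.5–1.9 deaths at one month, 8–10 at 6 months and 15–17 at 12 months. Each death scores mRS 6 and leaves no EQ-5D response.

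**Step 4. How a survival gain can hide a functional loss.** Take the 14-month median and a hazard ratio of 0.7 in the wider-resection arm. Deaths by 6 months are 25.7% against 1 − 2^(−0.7 × 6/14) = 18.8%, a gap of 6.9 points (9.3 against 6.8 of 36). Count as poor anyone dead or functionally worse. An excess of 6.9 points with surgical worsening among survivors of the wider resection would then leave the two arms equal. That is 6.9/81.2 = 8.5% of its survivors. At one month the corresponding gap in deaths is 4.8% against 3.4%, only 1.4 points.

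**Step 5. Dilution, with assumed rates.** Suppose surgery worsens function in 10% against 25% of patients, and a share d of the rest worsens from disease or death equally in both arms. The difference becomes 15 × (1 − d) points.

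| d | Arms | Difference | Power, 36 per arm |
|---|---|---|---|
| 0 | 10% vs 25% | 15 points | 39% |
| 20% | 28% vs 40% | 12 points | 19% |
| 50% | 55% vs 62.5% | 7.5 points | 9% |

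Late timing weakens the surgical signal without removing it. Even undiluted, the comparison is weak with 36 per arm.

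**The case against.** Several stronger conclusions are tempting, and the documents do not support them.

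- **Disease and death dominate the 6-month scores.** With no treatment effect, about 73–77% of patients are alive at 6 months, and no progression or adjuvant-toxicity rate is given. Mixing is shown; dominance is not. The 13–16 month median is also a general figure for high-grade glioma, while this trial selects patients with Karnofsky ≥ 60 and single tumors in safe locations, so mortality could be lower. Against that, 14 months is the sponsor's own planning value for the follow-on trial.
- **The pilot cannot show functional cost.** This ignores NIHSS at days 2 and 30, surgical adverse events, 30-day mortality and the neuropsychological tests, which are aimed at subtle differences from the wider resection. A randomized 6-month comparison also validly estimates the net, lasting effect. What stands is that the early measures are not measures of disability or quality of life, and that the neuropsychological tests are optional and unscheduled.
- **NIHSS is unsuitable because eloquent regions are excluded.** The protocol calls NIHSS validated and adopted in surgical trials. Doubting it on these grounds is inference.
- **The phase III decision turns on these scales.** The safety condition is that the DSMB raises no concern that cannot be rectified. The reports described under Interim analyses contain 30-day mortality and serious adverse events. No rule uses an mRS or EQ-5D contrast, and the pilot is descriptive.
- **Day 30 should be the main functional comparison.** Day 30 can include transient deficits. Choosing between early and lasting function is a choice of estimand, and the 6- and 12-month times also serve the cost-utility work and the test of retention.

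None of this supplies the missing day 30 or preoperative value.

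**Conclusion.** The point holds in a limited form. mRS and EQ-5D are presented as capturing the impact of deficits on function and quality of life, but neither is scheduled before surgery or within the first 6 months after it. Early functional cost is seen only indirectly, and the promised change from baseline cannot be computed from the scheduled data. These facts are read directly from the text and the schedule.

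The size of the mixing rests on exponential survival at the stated medians: about 23–27% dead at 6 months and 41–47% at 12 months, against 4–5% at one month. A hazard ratio of 0.7 lowers the 6-month figure to 18.8% at a 14-month median. The shares due to progression and adjuvant treatment cannot be computed from the documents. The 6- and 12-month assessments are not wrong; they answer a different question, the net longer-term effect. This is an inexpensive improvement to the schedule, not a flaw that invalidates the pilot.

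**What to change.** Add mRS and EQ-5D to the schedule at two existing visits:

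1. **Screening**, so that the change from preoperative baseline can be computed at every later assessment.
2. **Day 30 (± 5)**, where NIHSS is already done in person, so that deficit and functional impact are recorded together.

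Report the day 30 values and their change from baseline descriptively by arm, as the early functional safety measure. Keep 6 and 12 months as the net longer-term outcomes, and state there that they reflect surgery, disease, adjuvant treatment and death together. Amend the timings in Secondary outcomes and Participant timeline to match the table.

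The cost is the extra schedule entries, the matching case report form fields, and slightly longer screening and day 30 visits. No new visit is needed.
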